## 6.2 Withdrawals

For each period, the number of participants who withdraw from treatment, which also implies that they withdraw from the study, will be summarized by group, and primary reason for withdrawal, and by treatment group and all reasons for withdrawal.

Participants who withdraw will be listed for each period. The listings will include the number of days in the study until withdrawal, the date of first treatment, the date of the latest treatment prior to withdrawal, the number of days since latest treatment, the primary reason for withdrawal, all reasons for withdrawal.

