**3.4.2 Blinding/Unblinding**

The participants, outcome assessors, and the statistician will be blinded to treatment assignment. Unmasked personnel will include the dedicated investigator responsible for the randomization module. Because of the nature of the intervention, acupuncturists cannot be blinded, but they will be trained not to communicate with participants or outcome assessors about treatment procedures and responses.

In case of a serious adverse event (SAE) or pregnancy, or in cases when knowledge of the study treatment assignment is needed to make treatment decisions, the participants may unblind the treatment assignment as deemed necessary, mainly in emergency situations. When a blind is broken, the participant will be withdrawn from the study, and the event will be recorded onto the case report forms (CRFs). The circumstances leading to the breaking of the code should be fully documented in the investigator’s study files and in the participant’s source documentation. Treatment assignments should not be recorded in any study documents or source documents.

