**3.5 Withdrawal from Study**

Withdrawal of consent occurs when a participant does not want to participate in the study anymore, does not want any form of follow-up, or does not want any further study related contacts. Participants have the right to withdraw from the study at any time without prejudice to their future treatment.

If a participant withdraws consent, the investigator must make every effort to determine the primary reason for this decision. If the withdrawal is due to adverse events (AEs), refer to the **section 9**. Participants who have withdrawn from the study cannot be included again in the study.

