**9.4 Treatment and Follow-up Visits of Adverse Events**

Each patient is free to withdraw from the study at any time. The investigator can assess the subject's deterioration or AEs and determine whether the withdrawal from the trial is in the subject's best interest. Should a patient decide to withdraw after the administration of treatment, or should the investigator decide to withdraw the patient, all efforts will be made to complete and report all observations up to the time of withdrawal. A complete final evaluation at the time of the patient’s withdrawal should be made and an explanation given as to why the patient is withdrawing or being withdrawn from the study. And patients with AEs must be treated in accordance with usual clinical practice at the discretion of the investigator.

Non-serious AEs must be followed up until resolution or the completion/withdrawal visit, whichever comes first. At the completion/withdrawal visit, information on new AEs, if any, and stop dates for previously reported AEs must be recorded. SAEs that are spontaneously reported by a patient to the investigator after the completion/withdrawal visit must be handled in the same manner as SAEs that occur during the study. These SAEs will be recorded in the CRFs. The investigator must follow up on all SAEs until the event has resolved or stabilized, until the patient is referred to the care of a health care professional, or until a determination of a cause unrelated to the treatment or study procedure is made, and report to the principal investigator all relevant new information using the same procedures and timelines as those for the initial Serious Adverse Event Form.

Patients with a clinically significant out-of-range clinical safety laboratory test value at the completion/withdrawal visit must be followed in accordance with usual clinical practice. If the clinically significant out-of-range clinical safety laboratory test value has not normalized or stabilized or a diagnosis or a reasonable explanation has not been established by the investigator at the completion/withdrawal visit, the investigator must decide whether further follow-up visits are required (this may include an additional medical examination and/or additional blood sampling). If further follow-up visits are made, these must be documented in the patient’s medical records and not in the CRF.

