It is essential to collect as much data as possible for all participants throughout the study, especially all potential endpoint events. Discontinuation of study treatment does not mean discontinuation of follow-up or termination of study participation. Participants who have discontinued performance of study treatment are expected to, and should be encouraged to, remain in follow-up until the end of study.

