# 4. ANALYSIS SETS

## 4.1 Intention-to-treat Analysis Set

The Intention-to-Treat (ITT) analysis set will include all randomized participants. In this population, treatment will be assigned based on the treatment to which participants are randomized, regardless of which treatment they actually received.

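### SAP 6.2 treats stopping treatment as leaving the study, which contradicts Protocol section 14 and leaves the week-4 outcome of early stoppers open to unspecified imputation

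*Combined protocol and SAP*

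**What the plan says.** The documents give three rules on what happens to a participant who stops treatment.

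- SAP 6.2 (Withdrawals) summarises, by period and group, "the number of participants who withdraw from treatment, which also implies that they withdraw from the study".
- Protocol section 14 (Study Discontinuation) states: "Discontinuation of study treatment does not mean discontinuation of follow-up or termination of study participation". It expects such participants to "remain in follow-up until the end of study".
- Protocol 3.4.2 (Blinding/Unblinding) says: "When a blind is broken, the participant will be withdrawn from the study". The occasions it names are a serious adverse event, pregnancy, and other cases where the allocation is needed for treatment decisions.

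Protocol 3.5 describes leaving the study as a separate event tied to consent: "Withdrawal of consent occurs when a participant does not want to participate in the study anymore". Protocol 9.4 sets what is gathered when a patient withdraws or is withdrawn: "all efforts will be made to complete and report all observations up to the time of withdrawal", together with a full final evaluation at that point.

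On analysis, SAP 4.1 says: "The Intention-to-Treat (ITT) analysis set will include all randomized participants". SAP 8.2 bases the primary outcome on the diary mean for the last treatment week. It needs at least 4 of 7 daily reports, sets the weekly score to missing otherwise, and uses 10 imputed data sets. It states no imputation model, no missing-data assumption and no rule for data recorded after treatment stops. The sensitivity analysis in SAP 8.1 and 8.2.1 uses the per-protocol set.

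**The concern.** The SAP and the protocol cannot both be right about whether a participant who stops treatment is still in the study. The SAP says that it was prepared from protocol version 1.1, so the mismatch is not left over from an amendment.

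It matters because the primary outcome comes from one late window. A participant who is classed as withdrawn before recording four diary days in week 4 has no primary outcome value. People who stop early may well differ from those who complete, so how their missing value is filled can move the treatment difference. With 30 per arm, 10% is three people, and the planned difference is only 0.5 points on a 0-10 scale.

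Nothing in the plan would show how much the imputation matters. The per-protocol set requires completion of the study with no omissions in the treatment plan (SAP 4.2), so it removes these participants instead of testing the assumption made about them.

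**Working it through.** **The plan's own figure.** SAP 3.2 gives pilot reductions of 3.4 (SD 0.3) and 2.9 (SD 0.7), 90% power and alpha 0.05. The alternative in SAP 8.2.1 is two-sided.

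- Difference: 3.4 - 2.9 = 0.5.
- Root-mean-square SD: sqrt((0.3² + 0.7²)/2) = sqrt(0.29) = 0.5385.
- n per group = 2 × (1.960 + 1.282)² × 0.29 / 0.5² = 24.4, rounded up to 25, so 50 in total. Power at 25 per group is 90.7% (normal approximation).
- Loss allowance: 50 / 0.9 = 55.6, so 56. The planned 60 covers this.

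The stated 50 reproduces, and this point does not affect it.

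**What follows from each rule for someone who stops treatment in week 2.**

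1. Under Protocol section 14, the diary continues, the week-4 mean is observed, and SAP 8.2 uses it.
2. Under SAP 6.2 applied literally, the person has left the study. Protocol 9.4 then seeks data up to that date plus a final evaluation. A final evaluation in week 2 cannot supply a week-4 diary mean, so the value is missing and is imputed.
3. Under Protocol 3.4.2, if the blind is broken, the result is the same as in step 2, even if the participant would agree to keep the diary.

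In steps 2 and 3 the imputation model decides the value. Ordinary multiple imputation under missing at random borrows from participants of the same arm who were observed. If these are mostly people still on treatment, it tends to predict the outcome under continued treatment.

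**Illustration of size.** The documents give no discontinuation rates and no outcomes for stoppers, so these are assumptions: stoppers are imputed at their arm mean (3.4 or 2.9), and their true reduction is either 1.5 points smaller or zero. The 10% borrows the size of the plan's loss-to-follow-up allowance, which is not a discontinuation rate.

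Bias in the difference = p(acupuncture) × shortfall(acupuncture) - p(sham) × shortfall(sham), where the shortfall is the imputed minus the true reduction.

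| Stopping (acupuncture / sham) | Stoppers improve 1.5 less | Stoppers do not improve |
|---|---|---|
| 10% / 10% | 0.15 - 0.15 = 0 | 0.34 - 0.29 = +0.05 |
| 10% / 5% | 0.15 - 0.075 = +0.075 | 0.34 - 0.145 = +0.195 |
| 10% / 0% | +0.15 | +0.34 |
| 0% / 10% | -0.15 | -0.29 |

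As shares of the planned 0.5: +0.05 is 10%, +0.34 is 68%, and -0.29 is 58% in the other direction. An imputation model that used the diary weeks before stopping could give smaller values if those weeks already showed the poorer response.

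**The case against.** The best defence is that SAP 6.2 is a section on counting and listing. It does not tell sites to stop the diary or analysts to discard later data. Collection is governed by the protocol. Section 14 asks for as much data as possible on everyone, and Protocol 3.6 does not let a participant be declared lost before the study ends. SAP 8.2 uses all data from the ITT sample. If sites follow section 14, nothing is lost.

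That stands, and it rules out several stronger readings that a reader might infer.

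- **That the data will be lost.** This holds only if the rule in SAP 6.2 or Protocol 3.4.2 is applied in practice.
- **That stoppers will be imputed as if they had carried on.** That is a usual result of missing-at-random imputation, but the SAP states no model. It is a risk that the plan leaves open, not something that it specifies.
- **That the bias favours acupuncture by 30% to 68% of the planned effect.** Those figures need stopping in the acupuncture arm alone. No document gives rates by arm. Needling reactions could raise stopping with acupuncture, and lack of benefit could raise it with sham, which reverses the sign.
- **That the ITT analysis is defeated.** Imputation keeps every randomised participant in the set. The SAP 4.1 phrase "regardless of which treatment they actually received" concerns the arm in which a person is analysed, not data after stopping.

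The defence does not remove the contradiction. Protocol 9.4 ties data collection to withdrawal, so calling someone withdrawn has practical effect. Protocol 3.4.2 is a rule of conduct, not of reporting. The disposition summaries in Protocol 12.4 and SAP 6.1 also name no category for people who stop treatment and stay in the study, who are the people that section 14 describes.

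**Conclusion.** The point holds as a contradiction between the SAP and the protocol, with a second inconsistency inside the protocol between 3.4.2 and section 14. If SAP 6.2 or Protocol 3.4.2 is followed, participants who leave before week 4 would have no observed primary outcome. Their values would come from an imputation model that is not described, and no planned analysis would test it.

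The size and direction of bias are unknown. Under the assumptions shown, it runs from -0.29 to +0.34 on a planned difference of 0.5, and is 0 to 0.05 when stopping is equal between arms. The ends of that range require all stopping to fall in one arm and stoppers to have no improvement at all.

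This should be fixed before outcome data are lost, because diary days that are not recorded cannot be recovered. It does not invalidate the design.

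**What to change.** - **SAP 6.2:** in "the number of participants who withdraw from treatment, which also implies that they withdraw from the study", delete the part after the comma. Report treatment discontinuation and study withdrawal as separate events, here and in the disposition summary.
- **SAP 8.2:** state that diary and week-4 and week-8 data observed after treatment stops enter the ITT analysis, and name the imputation model for what is still missing.
- **Protocol 3.4.2 and section 14:** reconcile them so that breaking the blind is recorded but does not by itself end outcome collection, with study withdrawal reserved for withdrawn consent as in 3.5. Protocol 9.4 also lets the investigator withdraw a patient, so align its wording with that definition.
- **Optional:** one delta-adjusted imputation analysis for values that remain missing.

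None of this says when treatment should stop; it concerns only outcome collection and analysis. The cost is a few sentences in each document, plus continued follow-up contacts that section 14 already foresees. The sample size does not change.

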## 6.3 Demographics and Baseline Characteristics

Participant’s demographics and baseline characteristics, including age, gender, body-mass index, current employment status, education, marital status, annual income, and facial pain will be summarized for the ITT population. The baseline diary efficacy variables listed in **section 8.1**, jaw opening and movement measurement, GCPS total score, JFLS-20 total score, DASS-21 total score, PSQI total score, PPT, sEMG, and expectation assessment, will be summarized by treatment group for the ITT set.

## 6.4 Diary Compliance

At least 85% compliance of TMD diary is needed during the baseline period and 50% during the treatment and follow-up periods. And the compliance will be assessed every four weeks.

# 7. PROTOCOL DEVIATIONS

Protocol violations include enrolling participants in violation of key eligibility criteria designed to ensure a specific subject population, failing to collect data necessary to interpret outcomes, noncompliance to study treatment administration, or any other deviations that may have an impact on the processes put in place for the care and safety of the participants or compromise the scientific value of the trial.

# 8. EFFICACY ANALYSIS

**8.1 General**

The efficacy data for this study consist of TMD pain related responses (e.g., facial pain intensity) collected after a 4-week treatment or follow-up.

In addition, the following questionnaires will be used for the assessments of efficacy, physical functioning, emotional functioning and additional treatment outcomes during the study.

- Pain related index measured by pain intensity (VAS score) and ≥30%, ≥50% reduction in pain intensity.

- Physical functioning measured by GCPS (**Appendix A**) and JFLS-20 (**Appendix B**).

- Emotional functioning measured by DASS-21 (**Appendix C**) and PSQI (**Appendix D**).

- Additional treatment outcomes measured by PPT and sEMG

The primary analysis will be performed on the ITT set, and the sensitivity analysis will be performed on the PP set.

## 8.2 Primary Efficacy Variable and Analysis

For the purpose of this study, the change of pain intensity will be defined as the reduced score of weekly pain intensity (reported on a 0-10 VAS) from baseline to the last week of treatment period.

The primary statistical analysis to evaluate the primary hypothesis will use all data from the ITT analytical sample in a linear regression model. Mixed models will be used to analyze the treatment effect at Week 4.

The weekly pain intensity was calculated if a participant completed at least 4 of the 7 daily reports of pain intensity. For patients with missing days and fewer than 4 days of TMD diary data for 1 week, the weekly pain intensity was considered missing before the multiple imputation procedure. The statistics were based on 10 sets of imputed data, where the mean is the average of the means from the 10 data sets and the standard error (SE) of the mean is adjusted based on the imputation variance estimates.

### 8.2.1 Primary Efficacy Analysis

The hypothesis testing for the primary analysis is:

*H_0_: δ_1_=δ_2_*

*H_1_: δ_1_≠δ_2_*

where δ1 and δ2 are the estimates of weekly pain intensity change from baseline to the last week of treatment for the acupuncture group and the sham acupuncture group respectively.

The primary efficacy endpoint was the change from baseline in mean weekly pain intensity at week 4, the main analysis was performed using an analysis of linear regression model adjusted for sex, age, weekly pain intensity at baseline, TMD-specific medication. The LSM change from baseline with SE was presented for each treatment group, and the LSM with 95% confidence intervals (95% CIs) for the treatment differences, and associated p-values will be provided. A corresponding sensitivity analysis will be performed on the PP set using a linear regression model as specified for the primary efficacy outcome on the ITT set.

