**3. STUDY DESIGN**

**3.1 Overview of the Study Design**

This study is a single-blind, randomized controlled trial in China. The study will comprise a 1-week screening period, a 1-week baseline period, a 4-week treatment period, and a 4-week follow-up period.

An overview of the study is presented in **Figure 1**.

[figure not shown]

**Figure 1. Study design.** The study for each participant will be divided into 4 periods: a 1-week screening period, a 1-week baseline period, a 4-week treatment period and a 4-week follow-up period.

This study will include female and male participants, aged 18 to 80 years, suffering from temporomandibular disorder for at least three months before screening. Participants meet pain-related TMD and pain diagnosis of the Diagnostic Criteria of Temporomandibular disorders (DC/TMD). See Inclusion Criteria for further details on diagnosis.

The patients were allowed to take acute pain medications (nonsteroidal anti-inflammatory drugs, acetaminophen, or aspirin) prescribed by our dentist. We required that the same acute pain medication be used throughout the baseline period and the duration of the treatment period, which was documented throughout the course of the study. TMD-specific medication (corticosteroids, benzodiazepines, sedative hypnotics, muscle relaxants, opioids, antidepressants, and anticonvulsants) were disallowed throughout the study. Any new prescription medication, injection therapy for pain (e.g., tender or trigger point injections, steroid injections), acupuncture, biofeedback, transcutaneous electrical nerve stimulation (TENS), or oral splint should not be commenced for the management of pain throughout the study.

After completing the informed consent process at the end of screening period, participants will be screened for eligibility. Eligible participants will be randomly assigned in a 1:1 ratio to acupuncture group or sham acupuncture group.

Pain information will be captured daily during the entire study using a TMD diary. Additional assessments of physical functioning (measured by jaw opening and movement, Graded Chronic Pain Scale [GCPS] and Jaw Functional Limitations Scale-20 [JFLS-20]), the emotional functioning (measured by Depression, Anxiety and Stress Scales [DASS-21] and Pittsburgh sleep quality index [PSQI]), and additional treatment outcomes (PPT and sEMG) will be measured at the end of baseline, treatment period, and follow-up period (week 0, week 4, week 8).

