**Prior/Concomitant Therapy:**

• Have commenced occlusal splint therapy for the management of facial pain within 1 month prior to the screening period;

• Used any injection therapy (e.g., tender or trigger point injections, steroid injections) for the management of pain within 1 month prior to the screening period

• Used acupuncture, biofeedback, or TENS for the management of pain within 1 month prior to the screening period;

• Used TMD-specific medication (corticosteroids, benzodiazepines, sedative hypnotics, muscle relaxants, opioids, antidepressants, and anticonvulsants) intervention within 1 month prior to the screening and baseline period.

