**12.6.2 Primary Analysis of the Primary Outcome**

The linear regression model will be applied for the primary outcome (change from baseline in mean weekly pain intensity at week 4). The model will include treatment as fixed effect; Sex, age, weekly pain intensity at baseline, TMD-specific medication as covariates. The LSM change from baseline with standard error (SE) was presented for each treatment group, and the LSM with 95% confidence intervals (95% CIs) for the treatment differences, and associated p-values will be provided.

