### 8.3.2 Secondary Efficacy Analysis

For the proportion of responders of ≥30%, ≥50% reduction in pain intensity, a logistic regression model was implemented adjusted for sex, age, weekly pain intensity (VAS) at baseline, TMD-specific medication. Mean percentage with SE, and odds ratios with 95% CIs were presented for the efficacy outcomes by 4 weeks.

The analysis of continuous secondary outcomes were performed similarly to the primary efficacy outcome. A linear regression method, which is similar to the primary analysis setup, will be used for the analysis of secondary efficacy variables change from baseline to week 4: jaw opening and movement, GCPS score, JFLS-20 score, DASS-21 score, PSQI score, PPT, sEMG. The LSM change from baseline with SE was presented for each treatment group, and the LSM with 95% CIs for the treatment differences, and associated p-values will be provided.

A corresponding sensitivity analysis will be performed on the PP set using a linear regression model or logistic regression model as specified on the ITT set.

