### 8.4.3. Exploratory Efficacy Analysis

The analysis of change from baseline in mean weekly pain intensity, jaw opening and movement at week 8 are performed similarly to the primary efficacy outcomes. The change from baseline in GCPS score, JFLS-20 score, DASS-21 score, and PSQI score at week 8 will be analyzed using the linear regression method as described in **section 8.3.2**.

A corresponding sensitivity analysis will be performed on the PP set using a linear regression model or logistic regression model as specified on the ITT set.

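### The efficacy models adjust for TMD-specific medication, which the protocol bars before entry and on study: the term does nothing if the protocol is followed and can bias the treatment effect if it is not

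*Combined protocol and SAP*

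**What the plan says.** **The covariate.** Protocol 12.6.2 lists "Sex, age, weekly pain intensity at baseline, TMD-specific medication as covariates" for the primary outcome, and SAP 8.2.1 repeats the list, specifying a "linear regression model adjusted for sex, age, weekly pain intensity at baseline, TMD-specific medication". For the two responder outcomes, SAP 8.3.2 specifies that "a logistic regression model was implemented adjusted for sex, age, weekly pain intensity (VAS) at baseline, TMD-specific medication"; Protocol 12.6.3 matches it.

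The other models inherit the term by reference:
- The continuous secondary outcomes use "A linear regression method, which is similar to the primary analysis setup" (SAP 8.3.2).
- Pain and jaw movement "at week 8 are performed similarly to the primary efficacy outcomes" (SAP 8.4.3); the week-8 questionnaires point back to SAP 8.3.2.
- The per-protocol sensitivity analyses use the same models as the ITT set.

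The mixed-model sentence in SAP 8.2 names no covariates.

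**The drug rules.** Protocol 4.3 (Prior/Concomitant Therapy) excludes patients with TMD-specific medication "intervention within 1 month prior to the screening and baseline period". Protocol 3.1 lists the drug classes, ending with "opioids, antidepressants, and anticonvulsants) were disallowed throughout the study", and Protocol 5.2 repeats the rule. Protocol 6 collects this medication for the 30 days before screening and during the study.

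Permitted acute analgesics are a separate class, recorded in the daily diary, and appear in no model.

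**The concern.** A covariate helps only if it varies between participants and is fixed before randomisation. On a plain reading of the drug rules, this one fails one condition or the other. Full adherence makes it a column of zeros. On-study violations make it vary, but they happen after randomisation and may well follow poor pain relief. Adjusting for something that treatment can influence gives a contrast that randomisation no longer protects.

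At stake is the primary comparison in a 60-patient trial planned around a 0.5-point difference. Because the variable is undefined, its coding and window could also be chosen after the data are seen.

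**Working it through.** **1. The plan's own figure.** Inputs from SAP 3.2: mean reductions 3.4 (SD 0.3) and 2.9 (SD 0.7), alpha 0.05 (taken as two-sided, to match the hypotheses in SAP 8.2.1), power 90%.
- Difference = 3.4 - 2.9 = 0.5.
- Common SD = sqrt((0.3² + 0.7²)/2) = 0.539.
- n per arm = 2 × [0.539 × (1.960 + 1.282)/0.5]² = 24.4, so 25 per arm and 50 in total, as stated. Power at 25 per arm is 0.91 by the normal approximation and 0.90 by the t distribution.
- 60 randomised less 10% leaves 54, which covers the 50.

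This is an unadjusted comparison of two means. It uses no covariate and does not change if the term is removed.

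**2. Protocol followed.** The design matrix has six columns: intercept, treatment, sex, age, baseline pain, medication. With medication zero for all 60 participants the rank is 5 of 6. Only the medication coefficient is inestimable. Dropping the column leaves the treatment estimate as it was, with 60 - 5 = 55 residual degrees of freedom.

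**3. On-study use, same selection rule in both arms.** Assumptions for a simulation, none from the documents beyond the 0.5 and 0.539: 30 per arm, use more likely when improvement is poor, and no effect of the drug itself. The correlation between response and propensity to use is 0.5 (moderate) or 0.8 (strong). Mean adjusted differences:

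| Sham participants using | Correlation 0.5 | Correlation 0.8 |
| --- | --- | --- |
| 5% | 0.48 | 0.46 |
| 10% | 0.47 | 0.43 |
| 20% | 0.45 | 0.39 |

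Without the covariate the estimate stays at about 0.50. At 10% sham use the loss is (0.50 - 0.47)/0.50 = 6% to (0.50 - 0.43)/0.50 = 14%. At correlation 0.8, power falls from about 0.94 to 0.88. At correlation 0 the adjusted estimate stays at about 0.50.

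The rule acts in both arms, so some acupuncture participants also use the drugs. Their proportion is Φ(-1.282 - correlation × 0.5/0.539), which is Φ(-1.746) = 4% at correlation 0.5 and Φ(-2.024) = 2% at 0.8.

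**4. On-study use in the sham arm only.** If 3 of 30 sham and no acupuncture participants use the drugs, the indicator takes those three out of the contrast. The sham mean then rises by (3/30) × gap, where gap is the difference in mean response between sham non-users and users.
- Users exactly the worst three of 30, assuming normality: expected gap = 1.86 SD = 1.86 × 0.7 = 1.30 points. Shift = 0.10 × 1.30 = 0.13, and 0.13/0.5 = 26%. The adjusted difference is 0.37.
- Weaker selection scales the gap by the correlation. At 0.5: 0.5 × 1.30 = 0.65, shift 0.065, 13%. At 0.8: 0.8 × 1.30 = 1.04, shift 0.104, 21%.

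If the users were in the acupuncture arm, the same arithmetic would raise the acupuncture mean and inflate the difference.

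**The case against.** **The analysis does not fail.** A reader might infer that the primary model cannot be estimated. Step 2 shows otherwise: if nobody uses these drugs, software drops a redundant column and the result stands. This objection holds in full for the adherent case.

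**The covariate need not be post-randomisation.** Protocol 4.3 reaches back only one month, and Protocol 8.1.1 collects prior TMD treatment history, so older use could vary and would precede randomisation. So would an entry violation. Both are possible, so a reader should not conclude that the term must be either constant or post-randomisation. But neither document defines the covariate as older use, and the collection window in Protocol 6 coincides with the period in which use is barred.

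**Bias is conditional.** On-study use must occur, be coded into this variable and be related to response. The documents predict none of these, so they do not support saying that the randomised comparison is necessarily broken. With use concentrated in the sham arm, the bias is also toward no difference and would not create a false positive. That stands, but it does not cover use in the acupuncture arm.

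**The size can be overstated.** A reader might suppose a 1.5-point gap between sham non-users and users and arrive at 0.10 × 1.5 = 0.15, or 30% of the target. That gap exceeds the 1.30 points expected even if users were perfectly sorted by poor response.

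**Adjustment might be meant to remove the benefit of the prohibited drugs.** It does not do so reliably. Adding an assumed 0.5-point benefit to the step 3 simulation, at 10% sham use, gives unadjusted and adjusted differences of 0.47 and 0.47 at correlation 0.5, and 0.46 and 0.43 at correlation 0.8. Adjustment does not recover 0.50.

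**Conclusion.** The concern holds. The conflict between the covariate list and the drug rules is explicit, and nothing in either document gives the term a definition under which it would help. It is named in the primary and responder models and carried over by reference to the others. In the per-protocol set, eligibility violators are removed, so barred use before entry is constant there. Whether prohibited on-study medication also removes a participant from that set is not stated.

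With full adherence the cost is nil. With 10% of sham participants using these drugs, the loss ranges from about 6% to about 26% of the planned 0.5 points. The low end has the same moderate selection acting in both arms. The high end has only sham users, all of them the worst responders. These figures rest on assumed use rates, assumed selection, normal responses and the pilot SDs. The plan gives no expected rate of prohibited use.

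**What to change.** Delete TMD-specific medication from the models in Protocol 12.6.2 to 12.6.4 and SAP 8.2.1, 8.3.2 and 8.4.3, including the per-protocol analyses that inherit it. The analysis sections then agree with Protocol 3.1, 4.3 and 5.2.

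If a medication covariate is wanted, restrict it to a strictly pre-randomisation variable that can vary, and state its coding and window. Acute pain medication use in the 7-day baseline diary, as yes/no or days of use, would qualify and is already recorded. The documents do not show whether that was the intended covariate.

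Tabulate any on-study TMD-specific medication by arm as a protocol deviation, from the data collected under Protocol 6. SAP 7 has a broad deviations category but does not promise this table.

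The cost is wording in the protocol and SAP. No new data are needed, and the 50 evaluable and 60 randomised stay as they are.
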